**Methods:**

A web-based structured survey aimed at monitoring chronic pain and its effect on psychological functions will be delivered to patients with breast cancer through social media and email. In total, 42 patients with breast cancer affected by chronic pain will be recruited during the medical screening visit. The patients will be randomly divided into 3 treatment groups that will carry out either tDCS only, exercise therapy only, or a combination of both over a 3-week period. All the treatments will be delivered at the patients’ home through the use of a system including a tablet, wearable inertial sensors, and a tDCS programmable medical device. Using web-based questionnaires, the perception of pain (based on the pain self-efficacy questionnaire, visual analogue scale, pain catastrophizing scale, and brief pain inventory) and psychological variables (based on the hospital and anxiety depression scale and 12-item short form survey) will be assessed at the beginning of treatment, 1 week after the start of treatment, at the end of treatment, 1 month after the start of treatment, and 3 months after the start of treatment. The system’s usability (based on the mobile app rating scale and system usability scale) and its involvement in the decision-making process (based on the 9-item shared decision-making questionnaire) will be also evaluated. Finally, at the end of the treatment, a digital focus group will be conducted with the 42 patients to explore their unexpressed needs and preferences concerning treatment.

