To explore psychological variables and the individual impact of perceived pain, patients will be evaluated and receive a link with the questionnaires described in Table 1 at the following specific time points: before starting any treatments, 1 week after the start of the treatment, at the end of the 3 weeks of treatment, 1 month after the start of the treatment, and 3 months after the start of treatment. Furthermore, at the end of the treatment, each patient will be asked to answer questionnaires aimed at evaluating the usability of the system.

Finally, a focus group will be conducted with all the patients who took part in the study. The patients will be divided into groups of 14 participants based on the treatment group to which they were assigned. The aim of this investigation is to analyze the unexpressed needs, expectations, and preferences related to the home-based treatment. The focus groups will be conducted starting from a list of questions concerning the experience of the disease by the study participants, the relationship between the painful symptoms and the psychological significance, the expectations with respect to the treatment, and any difficulties encountered during the use of the technologies adopted during the rehabilitation program.

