### Sample Size

At least 42 patients with breast cancer will be recruited for the study. The patients will be divided into 3 experimental groups, each consisting of 14 patients, based on the type of treatment performed (tDCS only, exercise therapy only, or combined treatment). In case of dropouts, the recruitment of patients will continue until 42 participants complete the treatment.

Since the present study is the first to evaluate the effects of tDCS in patients with different types of chronic pain over a 3-week period, to estimate the expected difference between the effect of tDCS and combined therapy (tDCS and exercise therapy), for the calculation of the sample size we relied on a recently published study [54] of 45 patients with fibromyalgia to calculate the sample size. The published study compared the effects of tDCS and exercise therapy if carried out individually or in combination for 1 week. The improvements observed in the 3 treatment groups are shown in the Table 4.

**Table 4 table4:** Mean visual analogue scale (VAS) scores of the different treatment groups.

Treatment group	Baseline VAS	Improvement (%)	VAS at 1 week after treatment	ΔVAS (beginning of treatment vs 1 week after treatment)
tDCS^a^	7.2	18	5.904	1.296
Combined therapy	7.3	40	4.4019	2.8981
Exercise therapy	6.8	24	5.202	1.598

^a^tDCS: transcranial direct current stimulation.

The sample number for each individual clinical center was calculated to demonstrate the difference between the change in the visual analogue scale (VAS) value at the beginning of treatment and after 1 week of treatment between the group of patients receiving tDCS and that receiving combined therapy. A Wilcoxon-Mann-Whitney test was performed using G*Power V3 software [57] with an effect size of 1 and assuming the following parameters: a VAS change of 1.3 in the tDCS treatment group and 2.9 in the combined therapy group, as reported by Mendonca et al [54] in the evaluation after 1 week of treatment; an SD of 1.27 in both groups; a type 1 error of 0.05; and a power of 80%. A sample of the same size is adequate to demonstrate the difference in VAS between the exercise therapy group and the combined therapy group (based on data from Mendonca et al [54]).

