## Discussion

### Projected Impact

The present study protocol represents an innovative approach to the management of chronic pain in patients with breast cancer without the adoption of pharmacological treatments. Consistent with previous studies [15,59-62], we expect that the implementation of combined therapeutic interventions can directly produce a relevant improvement on pain relief.

Considering the beneficial effects of tDCS in increasing emotional well-being in psychiatric and neurological patients [63-65], we also assume that tDCS combined with telerehabilitation programs will reduce psychological distress and improve mental wellness in patients with breast cancer with chronic pain. Moreover, this interactive approach may motivate patients to increase treatment compliance, thus favoring better clinical outcomes.

Another key objective of this integrated home care strategy will focus on limiting the impact of physical and psychosocial symptoms associated with chronic pain on patients’ daily lives [4,7]. They represent significant barriers that can affect the ease of travel to health facilities and cause difficulties in accessing care treatments, with consequent economic and organizational impacts [66]. We hypothesize that the introduction of a home-based approach directly and continuously monitoring patients at home will allow us to assess disease progression and improve patients’ participation in routine clinical care, thus reducing disparities in accessing health care. Moreover, we expect to significantly optimize the rehabilitation session in terms of time and efficacy, thus reducing the direct and indirect health care and social costs.

Finally, the project aims to support patients affected by chronic pain through decision aids during critical moments of the therapeutic journey [67]. Telemonitoring of remote patients throughout the care process allows the evaluation of both clinical outcomes and patients’ reported opinions. Furthermore, the focus groups will allow a greater exchange of the preferences and perceptions of the treatment received by patients with breast cancer, highlighting the strengths and barriers that could have influenced their psychoemotional well-being and their overall experience with chronic pain [68]. We expect that focus group sessions will also contribute to examine adherence, identifying patients who need more personalized pain management strategies, and contextualizing the problem of unrelieved pain.

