### Study Limitations

A main limitation of the present study could be the personal use of the home care strategy. Despite the many advantages of this technological approach, some patients may find it difficult to use the equipment without direct assistance from a health care professional. The self-management of the home care strategy could also have a negative influence on treatment adherence, causing possible dropouts during the study phases. For these reasons, it will be necessary to monitor patients’ motivation during treatment to prevent patients from neglecting rehabilitation.

Patients should also be adequately informed of the possible risks linked to the administration of the treatments to reduce concerns about the occurrence of possible adverse effects of tDCS. In particular, adverse events could involve the appearance of local effects of the stimulation consisting of a slight burning sensation or skin redness. Nevertheless, it should be noted that participation in a trial involves strict control by the experimenter to limit any problems that may arise.

Furthermore, the initial recruitment via social media and email could orient the sample toward younger and technologically experienced patients. However, we adopted this instrument to promote the recruitment of patients throughout the country to overcome geographical barriers related to the access to health care. Additionally, due to the use of digital devices during the rehabilitation program proposed in this study protocol, the enrollment of technologically savvy patients with breast cancer could facilitate the use of the home-based treatment.

Finally, given the importance of subjective perception on the classification of pain, we chose to adopt several self-report tools to assess the personal experience of the patients with breast cancer. However, these instruments have limitations, as it is not possible to obtain objective information. When drawing conclusions, it will therefore be necessary to consider that the data may be influenced by various personal factors.

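### Focus groups are promised to everyone who took part but sized at 14 per arm, and the usability evidence would in effect come from completers, so it may lean favourable

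*Protocol article*

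**What the plan says.** - **Who is in the focus groups.** The Intervention section states that "a focus group will be conducted with all the patients who took part in the study". The following sentence reads: "The patients will be divided into groups of 14 participants based on the treatment group to which they were assigned". The Methods part of the Abstract puts the total at 42: "at the end of the treatment, a digital focus group will be conducted with the 42 patients".
- **What 42 means.** Under Sample Size: "In case of dropouts, the recruitment of patients will continue until 42 participants complete the treatment". So 42 is the number who finish treatment, and the number randomised is open-ended.
- **When usability is asked.** Intervention section: "at the end of the treatment, each patient will be asked to answer questionnaires aimed at evaluating the usability of the system". Table 1 lists two usability tools, the MARS and the SUS.
- **Who is analysed.** The Statistical Analysis section restricts the analysis to participants who complete the required treatment and removes those who do not complete every study phase.
- **Why this matters to the trial's own aims.** The Aims section includes acceptance of the technological approach. Study Limitations says that some patients may struggle with the equipment without direct help, and that self-managing the system could reduce adherence, "causing possible dropouts during the study phases".

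**The concern.** Acceptance and usability of a home system are questions on which the people who gave up are especially informative. Here, several rules point the same way. Dropouts are replaced, the focus group size matches the completer target, usability is asked when treatment ends, and dropouts leave the data analysis. No single rule says that only completers count, but together they leave little room for anyone else.

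The article also gives a reason why the missing people may differ: it names self-management of the system as a possible cause of dropout. If that happens, a favourable usability result could partly reflect who was left to answer. Separately, a reader cannot tell whom to invite to the focus groups, because the text gives two answers.

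**Working it through.** **Step 1. The plan's own figure.** 14 per arm × 3 arms = 42 (Intervention and Sample Size sections). This reproduces the 42 in the Abstract and equals the completer target. The focus group size is therefore the planned per-arm sample size, carried over.

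**Step 2. Consistency of the two focus group statements.** Let N be the number who took part and p the fraction who drop out. Recruitment stops when N × (1 − p) = 42, so N = 42 / (1 − p). Any p above 0 gives N above 42, and a focus group with everyone who took part no longer fits three groups of 14. The statements agree only when p = 0.

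**Step 3. How many people are affected.** The article gives no dropout rate, so p is an assumption, with N rounded up:

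| Assumed dropout | N = 42 / (1 − p) | Outside three groups of 14 | Share covered |
|---|---|---|---|
| 0% | 42 | 0 | 100% |
| 10% | 46.7, so 47 | 5 | 42/47 = 89% |
| 20% | 52.5, so 53 | 11 | 42/53 = 79% |
| 30% | 60 | 18 | 42/60 = 70% |

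**Step 4. Possible effect on the mean usability score.** Suppose dropouts would score g points lower than completers. The mean over all who started is (1 − p) × completer mean + p × (completer mean − g). Subtracting this from the completer mean leaves a difference of p × g. The gap g is a second assumption, taken on a 0 to 100 scale:

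| Assumed dropout | g = 0 | g = 10 | g = 20 | g = 30 |
|---|---|---|---|---|
| 10% (5/47) | 0 | 1.1 | 2.1 | 3.2 |
| 20% (11/53) | 0 | 2.1 | 4.2 | 6.2 |
| 30% (18/60) | 0 | 3.0 | 6.0 | 9.0 |

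A negative g would reverse the sign. The article's own remarks make a positive g the more plausible direction, but give no value.

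**Step 5. Does the usability wording rescue the dropouts?** The text says that each patient is asked, which is inclusive. But the stated time is the end of treatment, so a patient who stops in the first week has no clearly stated usability assessment. If that patient did give a score, the dropout exclusion under Statistical Analysis would remove it.

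**The case against.** Several objections carry weight.

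- **No sentence restricts these instruments to completers.** The Intervention section speaks of all who took part and of each patient, and Sample Size gives 42 as a minimum without a completer rule for each arm. A reader might infer that dropouts are barred by design. The article does not say so. The completer restriction is the combined effect of separate rules.
- **End of treatment may not be the only usability time point.** The MARS and SUS sit in Table 1, and the Table 1 questionnaires are sent at five time points, including one week after the start. Read literally, early leavers could supply a week-1 score. A usability score before any treatment makes little sense, so the text is ambiguous. In any case, the dropout exclusion would still apply to that score.
- **Bias is not certain.** It needs dropouts to occur and to hold worse views. Patients may stop for unrelated reasons, and Study Limitations says that motivation should be monitored. A reader might conclude that usability will be overstated; the documents support only that it may be.
- **Adherence.** Because the article expects that "focus group sessions will also contribute to examine adherence", a reader might infer that adherence too will be overstated. That does not follow. Exercise adherence is also monitored remotely and quantitatively in groups B and C, and the focus groups only add to it.
- **Focus groups give no estimate to inflate.** They are qualitative, ask about difficulties with the technology, and are analysed separately in T-Lab. The risk there is missing voices.
- **This is a condensed article.** Exit procedures may be in the full protocol, so their absence here is not held against it. The point rests on what the article does state: the conflicting group sizes, the timing, and the dropout exclusion.

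**Conclusion.** The concern holds in a limited form. The contradiction between inviting everyone and fixing 14 per arm is firm and appears with the first dropout. The completer selection in the usability and acceptance evidence follows from the replacement rule, the end-of-treatment timing and the dropout exclusion read together. Its direction is plausibly favourable, on the article's own account of why patients might stop.

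The size is not computable from the documents. At 10% to 30% assumed dropout and an assumed 20-point SUS gap it is about 2 to 6 points; across gaps of 0 to 30 points it runs from 0 to 9. This is a modest point that is cheap to repair. It does not bear on the pain comparison, and it gives no ground for saying that adherence will be overstated.

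**What to change.** 1. **Reconcile the focus group wording.** State whether the groups are for everyone who took part or for 42 completers, and give 14 per arm as a planned size, not a fixed one.
2. **Time the usability scales by event.** Send the SUS and MARS electronically at discontinuation or at the end of treatment, whichever comes first, and state whether they are also part of the five-time-point set.
3. **Exempt usability from the dropout exclusion.** Report it for all who started treatment, and separately by completion status.
4. **Hear from those who stopped** by inviting them to a focus group or by sending a short electronic exit question, without enlarging the sessions. With 14 people in 60 to 90 minutes, each has about 4.3 to 6.4 minutes (60/14 and 90/14). At 60 randomised, 20 per arm would have 3 to 4.5 minutes (60/20 and 90/20).

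The cost is one extra questionnaire link, using tablets and links that patients already have. Some dropouts will not respond, so the number who answered among those who stopped should be reported. The change has to be in place before patients begin to stop, because views at the point of stopping are hard to recover later.

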### Focus Group Meetings

A telematic platform will be used to carry out the focus group meetings at the end of the treatment. The duration of the focus group meetings will be between 60 and 90 minutes, and breaks will be provided every 45 minutes to avoid tiring the patients. Audio and video will be recorded from every meeting and subsequently analyzed using T-Lab software, which comprises several linguistic and statistical tools [56].

### Sample Size

At least 42 patients with breast cancer will be recruited for the study. The patients will be divided into 3 experimental groups, each consisting of 14 patients, based on the type of treatment performed (tDCS only, exercise therapy only, or combined treatment). In case of dropouts, the recruitment of patients will continue until 42 participants complete the treatment.

Since the present study is the first to evaluate the effects of tDCS in patients with different types of chronic pain over a 3-week period, to estimate the expected difference between the effect of tDCS and combined therapy (tDCS and exercise therapy), for the calculation of the sample size we relied on a recently published study [54] of 45 patients with fibromyalgia to calculate the sample size. The published study compared the effects of tDCS and exercise therapy if carried out individually or in combination for 1 week. The improvements observed in the 3 treatment groups are shown in the Table 4.

**Table 4 table4:** Mean visual analogue scale (VAS) scores of the different treatment groups.

Treatment group	Baseline VAS	Improvement (%)	VAS at 1 week after treatment	ΔVAS (beginning of treatment vs 1 week after treatment)
tDCS^a^	7.2	18	5.904	1.296
Combined therapy	7.3	40	4.4019	2.8981
Exercise therapy	6.8	24	5.202	1.598

^a^tDCS: transcranial direct current stimulation.

The sample number for each individual clinical center was calculated to demonstrate the difference between the change in the visual analogue scale (VAS) value at the beginning of treatment and after 1 week of treatment between the group of patients receiving tDCS and that receiving combined therapy. A Wilcoxon-Mann-Whitney test was performed using G*Power V3 software [57] with an effect size of 1 and assuming the following parameters: a VAS change of 1.3 in the tDCS treatment group and 2.9 in the combined therapy group, as reported by Mendonca et al [54] in the evaluation after 1 week of treatment; an SD of 1.27 in both groups; a type 1 error of 0.05; and a power of 80%. A sample of the same size is adequate to demonstrate the difference in VAS between the exercise therapy group and the combined therapy group (based on data from Mendonca et al [54]).

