**Conclusions:**

We expect that the combination of tDCS and telemedicine programs will reduce pain perceived by patients with breast cancer and improve their mental well-being more effectively than single interventions. Furthermore, we assume that this home-based approach will also improve patients’ participation in routine clinical care, reducing disparities in accessing health care processes. This integrated home care strategy could be useful for patients with breast cancer who cannot find relief from chronic pain with pharmacological treatments or for those who have limited access to care due to poor mobility or geographical barriers, thus increasing the patients’ empowerment and reducing health care costs.

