### Randomization

All patients who have signed the informed consent form will be assigned an alphanumeric identification code through which they will be registered in a management software. Randomization is an integral part of the patient registration process and will take place automatically through an integrated randomization block with a 1:1 ratio, and each participant will be randomly assigned by the use of “RAND” formula in Excel (Microsoft Corp) to 1 of the 3 treatment groups described in Table 2.

**Table 2 table2:** Description of the experimental groups.

Treatment group	Description
Group A (tDCS^a^)	Patients will be treated with only tDCS 3 times a week for 3 consecutive weeks.
Group B (exercise therapy)	Patients will be treated exclusively with exercise therapy for 2 or 3 days a week for 3 consecutive weeks, depending on the patient’s characteristics.
Group C (combined therapy)	Patients will be treated by combining tDCS with exercise therapy. They will be subjected to a cycle of tDCS 3 days a week for 3 consecutive weeks. On the days between 1 stimulation and another, the patients will carry out exercise therapy sessions.

^a^tDCS: transcranial direct current stimulation.

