### Statistical Analysis

To evaluate the efficacy of the treatments, a statistical analysis will be conducted on the clinical scales, functional tests, and questionnaires using a dedicated software. Data distribution will be evaluated using Shapiro-Wilk tests. In the case of a normal distribution, statistical significance will be evaluated by applying parametric *t* tests and ANOVA for repeated measures. In case the assumption of a normal distribution is not supported, a nonparametric Wilcoxon-Mann-Whitney test will be used. Statistical analysis will be performed on all participants who complete the treatment required by the protocol. Participants who do not complete all phases of the study (ie, dropouts) will be excluded from the data analysis. Furthermore, as suggested by recent scientific literature, Bayesian statistics will also be applied using JASP open-source software in order to better estimate the possible absence of an effect of therapeutic strategy [58]. In particular, intragroup comparison analysis will be assessed using repeated measures ANOVAs (within subjects, time factors). Comparison of the subgroups (n=14 per group) will be performed using parametric or nonparametric hypothesis tests depending on the normality of the data distribution and corrections of type 1 errors. Finally, correlations will be performed between the VAS, patient demographics, and clinical data. All secondary outcomes will be evaluated by descriptive statistical analysis. Analysis will be carried out using SPSS Statistics (version 27; IBM).

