### Conclusion

The Technopain protocol is a new home care strategy that combines computerized training rehabilitation, noninvasive neuromodulation, and remote telemonitoring via a web platform for the treatment of psychosocial and physical symptoms related to chronic pain in patients with breast cancer. In particular, this approach will evaluate the impact of chronic pain on patients’ quality of life and will offer a rehabilitation program that can favor the treatment of the greatest number of patients through home delivery. This trial will primarily evaluate the fluctuation of perceived pain by patients during and after treatments, evaluating which of the different types of treatments is the most effective between the single treatments or their combination. In particular, we expect that this study will provide a useful treatment for all patients who cannot find relief from chronic pain with pharmacological treatments. Our ultimate aim is to encourage the development of personalized telemedicine, which can provide daily clinical assistance to patients, eliminating the economic and geographical barriers related to the use of health services.

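### The 14 per arm is justified only for the VAS change after 1 week, not for the 3-week programme under test; separately, the rule for secondary outcomes needs reconciling

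*Protocol article*

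**What the plan says.** **Sizing.** The Sample Size section of the protocol article bases the group size on the "difference between the change in the visual analogue scale (VAS) value at the beginning of treatment and after 1 week of treatment", tDCS against combined therapy. The inputs are mean changes of 1.3 and 2.9, an SD of 1.27, a type 1 error of 0.05 and 80% power. They come from a published fibromyalgia study that treated for 1 week. The article says it borrowed these because this is the first study of tDCS over 3 weeks in different types of chronic pain. It adds that the same size suffices for exercise against combined therapy. Table 4 heads the source values "VAS at 1 week after treatment", while the text describes the same changes as measured after a week of treatment.

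**Programme and visits.** Table 2 (Randomization) says of the tDCS arm: "Patients will be treated with only tDCS 3 times a week for 3 consecutive weeks". The Intervention section schedules questionnaires before treatment, "1 week after the start of the treatment, at the end of the 3 weeks of treatment, 1 month after the start of the treatment"; a last set follows at 3 months.

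**Question.** The Conclusion states: "This trial will primarily evaluate the fluctuation of perceived pain by patients during and after treatments". The Abstract's Conclusions expect the combination to reduce pain and "improve their mental well-being more effectively than single interventions".

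**Analysis.** To evaluate efficacy, Statistical Analysis says "a statistical analysis will be conducted on the clinical scales, functional tests, and questionnaires using a dedicated software", followed by t tests, repeated-measures ANOVA or Wilcoxon-Mann-Whitney tests. It mentions type 1 error corrections for group comparisons without naming a method. Near its end it says: "All secondary outcomes will be evaluated by descriptive statistical analysis". It does not list which outcomes are secondary.

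**The concern.** The only contrast with a stated effect, SD and power falls one third of the way through treatment. The question is about the whole 3-week programme and what follows it. Four post-baseline visits could each be reported as the answer, and the sample size has been argued for only one of them. If the arms separate more or less by week 3, or if the spread of changes widens, the 80% in the article says nothing about the comparison readers will care about most.

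The secondary outcomes are a separate matter. Mental well-being is presumably measured by HADS and SF-12. If these are secondary, a descriptive summary by arm does not estimate a difference between arms, so it cannot support the expected superiority. If they are tested, the sentence making secondary outcomes descriptive is wrong.

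**Working it through.** **1. Position of the sized visit.** 3 sessions a week × 3 weeks = 9 tDCS sessions. After 1 week, 3 of 9 have been given, one third of the course.

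**2. The article's own figure.** Power of the Wilcoxon-Mann-Whitney test was approximated by a noncentral t with asymptotic relative efficiency 3/π = 0.955:
- noncentrality = d × √(n × 0.955 / 2)
- degrees of freedom = 2 × n × 0.955 − 2

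With n = 14 and the stated effect size d = 1, noncentrality is 2.585 on 24.7 degrees of freedom. Power is 80.8% one-sided at 0.05, and 14 is the smallest n reaching 80%. So 14 per arm reproduces one-sided. Two-sided at d = 1, power is 70% and 18 per arm are needed. Sidedness is not stated. The stated means and SD give a larger effect, (2.9 − 1.3) / 1.27 = 1.26; on that basis 12 per arm suffice two-sided and 14 give 88%.

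**3. Moving the contrast to week 3.** The documents give no 3-week difference or SD, so these values are an assumed range (combined versus tDCS, two-sided 0.05, Wilcoxon-Mann-Whitney, no correction):

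| Week-3 difference | SD | d | Power at 14 per arm | n per arm for 80% |
|---|---|---|---|---|
| 2.0 | 1.27 | 1.57 | 97% | 8 |
| 1.6 (unchanged) | 1.27 (unchanged) | 1.26 | 88% | 12 |
| 1.3 | 1.27 | 1.02 | 72% | 17 |
| 1.6 | 1.6 | 1.00 | 70% | 18 |
| 1.6 | 2.0 | 0.80 | 51% | 27 |
| 1.0 | 1.27 | 0.79 | 50% | 28 |

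**4. Both contrasts under a named correction.** Inputs are the Table 4 changes (tDCS 1.296, exercise 1.598, combined 2.8981), SD 1.27 and 14 per arm. The differences are 1.602 (d = 1.26) and 1.300 (d = 1.02). Holm for two contrasts at two-sided 0.05 tests the smaller p value at 0.025 and, if that is significant, the larger at 0.05. Simulated with t tests on normal data:
- combined versus tDCS: about 85%
- combined versus exercise: about 72%
- both: about 69%

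The same simulation with Wilcoxon-Mann-Whitney tests gives about 82%, 67% and 64%.

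**5. Tested or descriptive.** The opening of Statistical Analysis covers clinical scales, functional tests and questionnaires, assigns them significance tests and says the purpose is efficacy. The later sentence assigns all secondary outcomes to descriptive analysis. HADS, SF-12, PSEQ, PCS and BPI are among the questionnaires in Table 1. Whichever of them are secondary fall under both rules.

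**6. Source label.** The source study treated for 1 week. A value taken after that week of treatment and a value taken 1 week after treatment ended could be two different visits. The article uses both descriptions for the same numbers.

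**The case against.** The strongest reply is that the 1-week basis is disclosed and explained. No 3-week data were thought to exist, and borrowing the nearest available effect is ordinary practice. That stands as a reason for the source. It does not make week 1 the right visit for this trial's own sized contrast, and it does not supply the missing assumption that the effect carries to week 3.

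A reader might go further and infer that the trial has a designated confirmatory test at week 1 that fails to match its question. The documents do not support that: nothing calls the week-1 contrast primary or confirmatory, and it is used only to choose the sample size. Nor is low power at week 3 shown, since with the same difference and SD it is 88%.

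A reader might also infer that the error rate is uncontrolled. Testing three arm pairs at four visits without correction would give about 32% familywise error at an assumed between-visit correlation of 0.6 (36% at 0.4, 26% at 0.8). But the article plans type 1 error corrections. At correlation 0.6, Bonferroni over the three pairs gives 13%, and over all twelve tests 4%. The method is unnamed, which an article may leave to the full protocol or analysis plan.

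On secondary outcomes, the text does not say they are analysed only descriptively, and it does not list them. The conflict is therefore inferred from two overlapping rules, and it has no bearing on the time-point issue. The label difference in Table 4 cannot be settled without the cited source.

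Finally, the end of week 3 is not the only defensible primary visit. It is, however, the existing visit that closes the programme being evaluated.

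**Conclusion.** The point holds as two separate defects.

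First, 14 per arm is argued only for a visit one third of the way through the tDCS course, with no stated link to a primary time point and no stated assumption for week 3. The consequence depends on figures the documents do not give. Over the assumed range, uncorrected two-sided power for combined versus tDCS at week 3 runs from 97% down to about 50%, and is 88% if nothing changes. With both contrasts under Holm at two-sided 0.05 and the Table 4 values, the exercise contrast (72%) and the joint result (69%) fall below the stated 80%. Those figures assume normal changes, an SD of 1.27 in every arm and t tests.

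Second, the analysis section gives overlapping rules for secondary outcomes and leaves the mental well-being expectation without a clear between-arm comparison. This is a wording conflict with no numerical size.

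**What to change.** **Primary endpoint.** Name VAS change from baseline to the end of the 3-week treatment as primary. Test combined versus tDCS and combined versus exercise under a named correction, for example Holm at two-sided 0.05. Make VAS at 1 week, 1 month and 3 months secondary.

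**Sample size.** State that the 1-week difference and SD are assumed to hold at week 3. Restate power for each contrast and for both together, with the sensitivity range above, and state sidedness. Reconcile the Table 4 column label with the text.

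**Secondary outcomes.** List them. For HADS, SF-12, PSEQ, PCS and BPI, replace the descriptive rule with between-arm differences and 95% confidence intervals, labelled secondary.

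**Cost.** Edits to the Sample Size and Statistical Analysis sections, with no new visit or measurement. The real price is candour: the 1-week effect becomes an explicit assumption, and at 14 per arm the stated power drops to about 72% for combined versus exercise and 69% for both contrasts. The sponsor must either accept that or enlarge the trial.
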